**Breakthrough infection analysis:**

The population for breakthrough infection analysis will be based on the FAS population and exclude participants whose SARS-CoV-2 infection status during the end of the 2022 pandemic cannot be confirmed through follow-up. The **Demographic analysis** will be performed as above.

(1) Proportion of different breakthrough infection states

Based on follow-up data, the status of breakthrough infections among the participants will be statistically described, and the infection rate will be used as an intergroup categorical variable for comparison using Pearson’s chi-square test.

(2) Proportion of different types of breakthrough infection symptoms

The symptoms of symptomatic infected individuals will be statistically described and displayed as intergroup categorical variables.

(3) Duration of breakthrough infection symptoms (days)

The duration of symptoms will be statistically described using the duration as the classification criterion (if longer than 7 days) and compared as an intergroup classification variable.

(4) Correlation between infection and antibody titers

The infection status within the two groups will be statistically described, and the corresponding antibody titers will be presented as continuous variables. An intragroup comparison will be performed using the Mann–Whitney U test, and the corresponding medians and 95% CIs will be calculated.

(5) Correlation between symptom severity and antibody titers

Based on the classification criteria of whether the duration of symptoms is longer than 7 days, whether there is accompanying fever, and whether there are multisystemic symptoms, the infection symptoms of the two groups will be statistically described. The corresponding antibody titers will be considered continuous variables; the Mann–Whitney U test will be employed for the intragroup comparison, and the corresponding medians and 95% CIs will be determined .

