| Key eligibility criteria | **Inclusion criteria**   1. Signed informed consent; 2. In females, the urine pregnancy test was negative; 3. At least 6 months of follow-up was completed; 4. HBsAg, anti-HCV, HIV, treponema pallidum hemagglutination assay (TPHA) screening was negative; 5. Armpit temperature was ≤37.0℃; 6. The young group was aged 18–59 years, and the elderly group between 60–80 years.   **Exclusion criteria**   1. In females, the urine pregnancy test positive; 2. Pregnant or lactating women; 3. Known allergies to certain components of these two vaccines; 4. Patients with serious chronic diseases or advanced diseases such as high blood pressure, diabetes, asthma, thyroid disease, *etc*. which cannot be controlled by drugs; 5. Those suffering from thrombocytopenia, hemorrhagic disease or thrombotic disease; 6. Those with congenital or acquired angioedema/neuroedema; 7. Those with a history or family history of convulsions, epilepsy, encephalopathy, other progressive neurological diseases, and psychiatric disorders; 8. Lymphadenopathy； 9. Lymphoma, leukemia and other systemic malignancies; 10. Autoimmune disease; 11. Chronic diseases with cute exacerbation or acute infectious diseases and fever. |
| Study design | Study type: Prospective real-world interventional trial  Allocation: Open, non-randomized  Intervention model: Parallel group  Primary purpose: Prevention |
| Date of enrolment | July 1, 2021 |
| Target sample size | 300 (200 in the elderly group, 100 in the young group) |
| Recruitment status | Recruited |
| Primary outcomes | **Primary endpoint measures**   - Safety profiles within one month after each vaccination dose, including:   1. The incidence of adverse events;   2. Liver function;   3. Kidney function;   4. Blood glucose;   5. Blood lipids. - The definition and grade of adverse events (AEs) were evaluated according to the Common Terminology Criteria for Adverse Events (CTCAE), version 5.0:  1. Grade 1 (mild) - asymptomatic or mild symptoms, clinical or diagnostic observations only, intervention not indicated; 2. Grade 2 (moderate) - minimal, local, or non-invasive intervention indicated, limiting age-appropriate instrumental activities of daily living (ADL); 3. Grade 3 (severe or medically significant but not immediately life-threatening) - indication for hospitalization or prolongation of hospitalization, disabling and limiting self-care ADL. |

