### 3.4.2 Secondary endpoint measures

- Immune protection of the participants:
  - - The titers of neutralizing and anti-receptor binding domain (RBD) antibodies at the baseline and the 1^st^, 2^nd^, 4^th^, 7^th^, 8^th^, 10^th^, 13^th^, and 16^th^ months after the first vaccination in each study group.

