## 3.5. Participant timeline

Figure 1. The schedule of enrolment, interventions, and assessments.

| **Visits** | **Screening** | **V1** | **V2** | **V3** | **V4** | **V5** | **V6** | **V7** | **V8** | **V9** |
| --- | --- | --- | --- | --- | --- | --- | --- | --- | --- | --- |
| **Timepoint (month)** | **Day**  **-21~0** | **Day 0** | **1^st^** | **2^nd^** | **4^th^** | **7^th^** | **8^th^** | **10^th^** | **13^th^** | **16^th^** |
| **Time window (day)** |  | **± 3** | **± 3** | **± 15** | **± 15** | **± 3** | **± 15** | **± 15** | **± 15** | **± 15** |
| **ENROLMENT:** | | | | | | | | | | |
| Informed consent | × |  |  |  |  |  |  |  |  |  |
| Eligibility screen | × |  |  |  |  |  |  |  |  |  |
| Demographical characteristics | × |  |  |  |  |  |  |  |  |  |
| Medical history | × |  |  |  |  |  |  |  |  |  |
| Urine pregnancy test  (reproductive women) | × |  | × | × | × | × | × | × | × | × |
| Height, weight, blood pressure | × |  |  |  |  |  |  |  |  |  |
| Underarm temperature | × |  |  |  |  |  |  |  |  |  |
| Lab tests & Images*^#^* | × |  |  |  |  |  |  |  |  |  |
| **INTERVENTIONS:** | | | | | | | | | | |
| Allocation |  | × |  |  |  |  |  |  |  |  |
| Vaccination |  | × | × |  |  | × |  |  |  |  |
| 30 minutes’ observing |  | × | × |  |  | × |  |  |  |  |
| **ASSESSMENTS:** | | | | | | | | | | |
| Lab tests*** | × |  | × | × | × | × | × | × | × | × |
| Distribute/recycle diary cards |  | × | × | × | × | × | × | × | × | × |
| Safety (AEs) |  | × | × | × | × | × | × | × | × | × |
| Safety (SAEs) |  | × | × | × | × | × | × | × | × | × |
| Concomitant care |  | × | × | × | × | × | × | × | × | × |
| Humoral immunoassays |  | × | × | × | × | × | × | × | × | × |

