# Including hepatitis B serologic, alpha-fetoprotein (AFP), carcinoembryonic antigen (CEA), Anti-HCV, HIV antibody, TPHA, electrocardiogram (ECG), chest x-ray, abdominal ultrasound (liver, gallbladder, spleen, pancreas, kidney). * Including liver and kidney function, blood glucose, and blood lipids.

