## 3.11. Safety/harms

AEs and SAEs will be monitored and recorded from the time the participant signed the informed consent form to the completion of the follow-ups. AEs/SAEs will be recorded in detail, including onset date, duration, severity, treatment, and relation to the investigational medical product. All AEs/SAEs will be followed up until finalized (recovery/relief, stability, death, or other explainable circumstances, such as lost to follow-up).

Once identified, SAEs must be acted upon and reported within 24 hours. They will be reported to the Institutional Review Board (IRB) as soon as possible.

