## 4.7. Ancillary and post-trial care

The investigators will continue to follow up with participants until the 19^th^ month for safety and research purposes. Long-term data regarding efficacy and safety will be collected.

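### The end-of-2022 infection comparison has no scheduled infection record: Figure 1 stops at month 16, the month-19 follow-up is not in it, and participants with unconfirmed status are dropped

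*Protocol*

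**What the plan says.** Section 3.10.2, under Breakthrough infection analysis, plans five analyses: infection status by group, symptom types, symptom duration split at 7 days, titres by infection status, and titres by symptom severity (duration, fever, multisystem involvement). The population is the full analysis set, from which the analysis will "exclude participants whose SARS-CoV-2 infection status during the end of the 2022 pandemic cannot be confirmed through follow-up". The text does not say what confirms a status.

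The trial summary gives a single enrolment date: "Date of enrolment | July 1, 2021". The last antibody time point is month 16 ("and 16^th^ months after the first vaccination in each study group"), which is also the last visit in Figure 1 (V9, ±15 days).

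Figure 1 has rows for adverse events, serious adverse events and diary cards ("Distribute/recycle diary cards") from V1 to V9. It has no row for a SARS-CoV-2 test or for infection status. The repeated laboratory tests are described as "Including liver and kidney function, blood glucose, and blood lipids".

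Two other sections bear on the period after V9. Section 4.7 states: "The investigators will continue to follow up with participants until the 19^th^ month for safety and research purposes", and adds: "Long-term data regarding efficacy and safety will be collected". Section 3.11 states: "AEs and SAEs will be monitored and recorded from the time the participant signed the informed consent form to the completion of the follow-ups"; those records include onset, duration and severity.

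**The concern.** The analysis needs infection status, symptom type, fever and symptom duration in days for a specific calendar period. For the first enrollees that period lies after the last scheduled visit. The month-19 follow-up reaches it, but it is not in the schedule, and nothing says what is recorded there about infection or symptoms. A diary card handed out at V9 would have no listed visit at which to be returned.

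The population rule adds to this. Keeping only participants whose status can be confirmed makes inclusion depend on the outcome. If infected and uninfected people differ in how easily they are confirmed, and if that differs between older and younger participants, the age comparison of infection partly reflects confirmability. The comparisons of titre by infection status and by severity use the same selected set.

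A related gap affects participants enrolled later, whose V9 may fall during or after the end of 2022. Without dated infections, month-16 titres raised by infection cannot be told apart from titres due to vaccination alone.

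**Working it through.** The protocol gives no power, event or rate figure for this analysis, so there is none to reproduce. The check is calendar arithmetic followed by bounds.

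**Step 1: dates.** Inputs are the enrolment date (trial summary), month 16 ±15 days (Figure 1) and month 19 (section 4.7). The first dose is taken to be on the enrolment date. The infection period is read as the end of calendar year 2022, because the protocol gives no exact dates. Only July 1, 2021 comes from the document; the later dates are assumptions, since no last-enrolment date is stated.

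| First dose | Month 16 | Window ±15 days | Month 19 |
| --- | --- | --- | --- |
| July 1, 2021 | Nov 1, 2022 | Oct 17 to Nov 16, 2022 | Feb 1, 2023 |
| July 31, 2021 | Nov 30, 2022 | Nov 15 to Dec 15, 2022 | Feb 28, 2023 |
| Aug 31, 2021 | Dec 31, 2022 | Dec 16, 2022 to Jan 15, 2023 | Mar 31, 2023 |
| Sep 30, 2021 | Jan 30, 2023 | Jan 15 to Feb 14, 2023 | Apr 30, 2023 |

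For the first enrollees V9 precedes the end of 2022. For later enrollees it may not. Month 19 falls on or after February 1, 2023 for everyone enrolled from July 1, 2021, so the follow-up in section 4.7 spans the period for all.

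**Step 2: what is recorded.**
- V1 to V9: adverse events and diary cards, but no infection item or test.
- After V9: general adverse event recording to the end of follow-up (section 3.11) and unspecified efficacy and safety data (section 4.7).
- No scheduled visit, diary return or infection form after V9.

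**Step 3: effect of the exclusion.** Let u be the share of the full analysis set whose status is unconfirmed and p the infection rate among those confirmed. The rate in the full set then lies between (1 − u)p, if none of the unconfirmed were infected, and (1 − u)p + u, if all were. Both u and p are assumed.
- u = 10%, p = 50%: 0.90 × 0.50 = 45%, and 45% + 10% = 55%.
- u = 30%, p = 50%: 0.70 × 0.50 = 35%, and 35% + 30% = 65%.

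**Step 4: effect on the age difference.** Suppose both groups show 50% and have the same u. Counting all unconfirmed participants as infected in both groups, or as uninfected in both, leaves the difference at zero. Counting them as infected in one group and uninfected in the other gives 55% − 45% = 10 points at u = 10%, and 65% − 35% = 30 points at u = 30%. These are outer limits, not expected biases.

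**The case against.** Several points on the other side are sound.

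- A reader might infer that no visit records symptoms. The protocol does not support that. Diary cards and adverse event recording are scheduled at V1 to V9, and section 3.11 records adverse events with onset and duration until follow-up is complete. A symptomatic infection could enter through that route. A dedicated infection item is what is missing; asymptomatic infection has no evident route.
- A reader might infer that follow-up ends before the period of interest. It does not: section 4.7 carries it to month 19. What stands is that this contact is absent from Figure 1 and has no stated infection or symptom content.
- A reader might infer that the outcome rests on recall. The protocol says only that status is confirmed through follow-up. Recall is one possible source; the actual source is unstated.
- A reader might attach a particular spurious age gap to the exclusion. Nothing in the protocol fixes its size or direction. If infected people are easier to confirm in both groups, much of the bias cancels. With an assumed true rate of 60% in both groups, and 95% of infected and 80% of uninfected young participants confirmed, the observed rate is 0.57/(0.57 + 0.32) = 64.0%. With 90% and 80% in the elderly it is 0.54/(0.54 + 0.32) = 62.8%, a gap of about 1 point.
- Breakthrough infection is not a listed primary or secondary endpoint, and confirmation rules or sensitivity tables can be left to a statistical analysis plan. That lowers the weight. But an analysis plan cannot create a contact, a form or a diary return; those belong in the protocol's schedule.
- Dropping unknown statuses fits the no-imputation approach of section 3.10.1. That rule names demographic, safety and immunogenicity data, and a bounding table can sit beside a complete-case analysis without replacing it.

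**Conclusion.** The point holds in a limited form. The protocol plans between-group comparisons of infection and symptoms at the end of 2022. Its schedule has no infection item and stops at month 16, which is October 17 to November 16, 2022 for the first enrollees. The month-19 follow-up that would cover the period is promised but neither scheduled nor given infection content. Participants are then excluded according to whether the outcome can be confirmed.

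The resulting bias is possible but of unknown size. For an observed 50%, the group rate is bounded at 45% to 55% with 10% unconfirmed and at 35% to 65% with 30% unconfirmed. The conclusion assumes that first doses began on the stated enrolment date and that the infection period is the end of calendar 2022. The share of participants whose V9 preceded that period is unknown, because no last-enrolment date is given. This is a worthwhile, inexpensive improvement to a supplementary analysis; it does not touch the primary safety comparison.

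**What to change.** 1. Enter the month-19 contact of section 4.7 in Figure 1 as V10 for both groups, with a fixed record: infected or not, date, basis of confirmation, symptoms, fever, and symptom start and end dates.
2. Hand out a diary card at V9 for return at V10.
3. Record dated infections at V2 to V9, so that titres measured after infection can be identified.
4. Report the number of participants with unconfirmed status by age group.
5. Show the infection-rate comparison with unconfirmed participants counted as all infected and as all uninfected. Include the two crossed assignments (infected in one age group, uninfected in the other), because step 4 of the working shows that treating both groups alike can leave the difference unchanged.

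The cost is one more diary card, a short form at a contact already promised, and one extra table. If data collection is already complete, items 4 and 5 can still be done from existing records, together with a statement of what counted as confirmed and when and how each status was obtained.

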### 3.3.2. Intervention assignment

Both the experimental and control groups will receive two doses of the inactivated COVID-19 vaccine, administered on day 0 (baseline) and day 25±3. A third booster dose will be given 6 months after the second dose.

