## 3.6. Sample size

The target sample size is 300 participants. The allocation ratio will be 2:1, with 200 participants in the elderly experimental group (aged 60–80) and 100 participants in the younger control group (aged 18–59).

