## 3.8. Allocation and vaccine management

### 3.8.1. Allocation

The participants will be assigned to either the experimental or control group in a 2:1 ratio based on age.

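### The end-2022 infection comparison between age groups is an unadjusted chi-square that cannot separate age from months since the booster, should these differ between the groups

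*Protocol*

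**What the plan says.** Section 3.10.2, Breakthrough infection analysis, item (1), states that "the infection rate will be used as an intergroup categorical variable for comparison" by Pearson's chi-square. It names no covariate, stratum or offset. The population is the FAS, restricted to those with known status in one calendar period: the plan will "exclude participants whose SARS-CoV-2 infection status during the end of the 2022 pandemic cannot be confirmed through follow-up".

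Vaccination runs on each participant's own clock. Section 3.3.2 has the first two doses "administered on day 0 (baseline) and day 25±3", and then "A third booster dose will be given 6 months after the second dose". Under section 3.8.1, participants are "assigned to either the experimental or control group in a 2:1 ratio based on age". The Trial Summary confirms that allocation is open and non-randomised. It gives July 1, 2021 as the date of enrolment, with no closing date and no dates by group.

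Two other parts of section 3.10.2 could have dealt with time since the booster, but do not. The demographic analysis, which the breakthrough section reuses, lists age, gender, BMI, laboratory indices and comorbidities, but no dose date. The general text on logistic regression screens baseline characteristics without naming an outcome, and months since dose 3 is not a baseline characteristic.

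**The concern.** Exposure comes in one calendar window and the booster date follows the enrolment date, so each month of later enrolment takes about one month off the interval from booster to wave. Randomisation would balance that interval on average; a split by age does not. If the two age quotas filled at different times, the groups would meet the wave at different distances from their last dose.

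Waning after vaccination is close to the trial's own question, since antibody titres are followed to month 16. If infection risk rises with time since the booster, the group enrolled earlier would show more infections for that reason alone. The chi-square would report this as a difference between age groups, or would hide a real one if the imbalance ran the other way. Because the planned demographic table has no dose date, a reader could not see the imbalance either.

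**Working it through.** **Plan's own figures.** The protocol gives no infection rate, effect size or power for this comparison, so there is no stated result to reproduce. The group sizes agree with each other: 200 + 100 = 300, ratio 2:1.

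**Date arithmetic.** Day 0 on July 1, 2021, plus 25 days and 6 months, puts dose 3 in late January 2022. That is about 10 months before December 1, 2022 and 10.6 months before December 15, 2022. Counting to December 15, enrolment 1, 2, 3 or 4 months later gives 9.7, 8.6, 7.7 or 6.6 months. The ±3-day vaccination windows move this by days only. What matters is the enrolment spread and whether it differs between the groups; the protocol states neither.

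**Assumptions for the illustration (none from the protocol).** No true age effect; 70% infected in the group with the shorter interval; infection odds multiplied by 1.10 to 1.20 per month since dose 3; a gap of k months between the group means; all 200 and 100 participants analysed.

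**Formulas.**
- Risk in the group with the longer interval: odds = (0.7/0.3) × OR^k, and p₂ = odds/(1 + odds). The other risk is p₁ = 0.7.
- With d = p₂ − p₁ and pooled risk p̄: SE₀ = √[p̄(1 − p̄)(1/100 + 1/200)], and SE₁ = √[p₁(1 − p₁)/n₁ + p₂(1 − p₂)/n₂].
- Probability of P < 0.05, two-sided: Φ((d − 1.96·SE₀)/SE₁) + Φ((−d − 1.96·SE₀)/SE₁). This is the normal approximation to the chi-square without continuity correction.

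**One case in full.** OR 1.20, k = 2, young group with the shorter interval (n₁ = 100, n₂ = 200):
- odds = 2.333 × 1.44 = 3.36, so p₂ = 0.771 and d = 0.071.
- p̄ = (100 × 0.700 + 200 × 0.771)/300 = 0.747, SE₀ = 0.0532, SE₁ = 0.0546.
- First term: (0.0706 − 0.1043)/0.0546 = −0.62, giving 0.268. Second term: about 0.001. Total: about 27%.

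**All cases.**

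| Gap in means (months) | OR per month | Risk, longer interval | False positive, young shorter | False positive, elderly shorter |
|---|---|---|---|---|
| 0 | any | 70.0% | 5.0% | 5.0% |
| 1 | 1.10 | 72.0% | 6.6% | 6.3% |
| 1 | 1.20 | 73.7% | 10.7% | 9.8% |
| 2 | 1.10 | 73.8% | 11.2% | 10.3% |
| 2 | 1.20 | 77.1% | 26.9% | 24.5% |
| 3 | 1.10 | 75.6% | 18.7% | 17.0% |
| 3 | 1.20 | 80.1% | 49.9% | 46.3% |

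The range is therefore about 6-11% for a 1-month gap and 10-50% for 2-3 months. A different waning assumption moves it a good deal. If risk rises by 1 to 5 percentage points per month from the same 70%, with the young group at the shorter interval, the rates are 5.4-15.6%, 6.7-48.9% and 8.7-84.9% for gaps of 1, 2 and 3 months.

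**The case against.** The strongest objection is that the premises of a bias are not in the protocol. A reader might infer that enrolment was rolling over many months. The protocol gives a single date, and some spread for 300 people at two hospitals is plausible but not stated.

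A reader might also infer from the January 26, 2022 entry in the revision history that enrolment ran to about the end of 2021, which would leave the last participants only some 4 months past dose 3 when the wave came. That reading fits poorly. Someone enrolled about January 1, 2022 would be due dose 2 on about January 26, the date of the amendment itself. Yet the entry already reports participants' experience after two doses, and it changes testing from month 7. For a July 1, 2021 start, month 7 falls on February 1, 2022, a few days after the amendment. The dates fit a more compact enrolment better, without proving it.

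Nor does spread alone bias the comparison; the mean interval must differ between the age groups. Both are recruited at the same two hospitals on the same schedule, and nothing in the protocol indicates a gap. All of this stands, and it limits the point to a possibility.

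It can further be said that a chi-square is a valid test of crude rates, that item (1) does not say a difference will be attributed to age, that age groups may differ in many other ways, and that adjusting an exploratory comparison is usually left to the SAP. The first three are fair, and they are why the chi-square can stay as a description. The last has less force, because the protocol does not leave the test open: it names an unadjusted one and lists the variables to be compared without a dose date.

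**Conclusion.** The concern holds in a limited form. The protocol fixes an unadjusted comparison of two non-randomised age groups for an outcome set in calendar time, while the booster date follows individual enrolment. If months since the booster differ between the groups, the planned test cannot separate that difference from age, and nothing else in the protocol does so.

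A reader might go further and conclude that the comparison is biased, or that its error rate is as high as 50%. The document does not support this. The existence and size of a gap are unknown; with equal mean intervals the error rate stays at 5%. The figures of 6-11% and 10-50% rest wholly on the assumed gap, waning rate and infection rate. They also use the full 200 and 100, although the FAS requirement of three doses and the exclusion of unconfirmed infection status can only reduce those numbers.

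The point is minor, since breakthrough infection is neither a primary endpoint (section 3.4.1) nor a listed secondary one (section 3.4.2). It is worth making because the remedy is nearly free.

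**What to change.** In the breakthrough infection analysis:

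1. Add months from dose 3 to a fixed date, such as December 1, 2022, to the demographic table, by age group.
2. Keep the Pearson chi-square in item (1), labelled as the crude, descriptive comparison.
3. Add a logistic regression of infection on age group with months since dose 3 as a covariate, and report the adjusted risk difference between age groups with its 95% CI.

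The FAS excludes anyone without all three doses, so everyone in this analysis should have a dose-3 date and no new data are needed. The cost is a few lines of wording, one extra model term and slightly wider intervals. If the table shows equal intervals, the adjusted result should be close to the crude one. If it shows little overlap between the groups, the adjusted estimate relies on extrapolation, and the report should say so.

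### The breakthrough-infection analyses do not require the antibody titre to precede the infection it is related to, and they reduce symptom duration to a 7-day cut

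*Protocol*

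**What the plan says.** All places are in the protocol.

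- **Section 3.10.2, Breakthrough infection analysis, item (4):** "The infection status within the two groups will be statistically described, and the corresponding antibody titers will be presented as continuous variables". The test is stated next: "An intragroup comparison will be performed using the Mann–Whitney U test". Item (5) treats titres the same way, by symptom class (duration over 7 days, fever, multisystem symptoms).
- **Section 3.10.2, Pseudovirus neutralization test analysis, item (1):** the same construction for pVNT50, with a nested t-test.
- **Population for the breakthrough analysis:** the FAS, with one further rule, to "exclude participants whose SARS-CoV-2 infection status during the end of the 2022 pandemic cannot be confirmed through follow-up".
- **Section 3.4.2:** titres at baseline and at months 1, 2, 4, 7, 8, 10, 13 and 16, counted as "months after the first vaccination in each study group". Section 3.5 gives the month-16 visit a window of ±15 days.
- **Section 1:** the only calendar entry for recruitment is "Date of enrolment | July 1, 2021". No closing date is given.
- **Section 4.7:** follow-up continues to month 19. No titre is scheduled there.
- **Breakthrough infection analysis, item (3):** symptom duration is headed in days but handled "using the duration as the classification criterion (if longer than 7 days"), as a two-class variable compared between groups.

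**The concern.** A titre can be read as a correlate of protection only if it was measured before the infection. A sample drawn afterwards also contains the response to that infection, so it pushes the infected group's titres up and works against any protective association. With up to nine titres per participant and no visit named, the text allows such samples to be used. It also leaves the visit to be chosen once the data are known.

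Month 16 is the visit at risk because it lies closest to the end of 2022. Its titres also feed a listed secondary endpoint, the between-group comparison at each visit. If the share of post-infection samples differs between the elderly and the young, part of a month-16 difference could reflect infection and not persistence of the vaccine response.

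The duration cut is a separate and smaller matter. It discards information in an analysis already confined to symptomatic cases.

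**Working it through.** The protocol states no power, event count or effect size for these analyses, so there is no figure to reproduce.

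**1. Does any rule exclude a post-infection titre?** The FAS drops participants without all three doses. The PPS drops those with six or fewer follow-ups. The breakthrough population drops those with unconfirmed infection status. The secondary analysis compares titres at each visit without regard to infection. None of these rules concerns the order of sample and infection.

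**2. Calendar.** Month-16 window = dose-1 date + 16 months ± 15 days. The start of the wave is assumed to be 1 December 2022; the protocol gives only the end of 2022.

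| Dose 1 (2021) | Month-16 window |
|---|---|
| 1 July | 17 Oct – 16 Nov 2022 |
| 16 July | 1 Nov – 1 Dec 2022 |
| 22 July (screening on 1 July + 21 days) | 7 Nov – 7 Dec 2022 |
| 1 August | 16 Nov – 16 Dec 2022 |
| 1 September | 17 Dec 2022 – 16 Jan 2023 |

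The limiting date is 1 December 2022 − 15 days − 16 months = 16 July 2021. For month 13 it is 1 December 2022 − 15 days − 13 months = 16 October 2021. If the wave is taken to start on 31 December 2022, the month-16 limit moves to 16 August 2021.

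**3. Effect on the association.** All inputs here are assumptions: normal titres in SD units, odds ratio for infection 0.5 per SD, 50% infected, and a fixed boost added for infected participants sampled after infection. The measure is the Mann-Whitney probability P(infected titre > uninfected titre). The null value is 0.50, and values below it mean protection.

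| Share of infected sampled after infection | Boost 1 SD | Boost 2 SD |
|---|---|---|
| 0% | 0.32 | 0.32 |
| 10% | 0.35 | 0.38 |
| 25% | 0.40 | 0.46 |
| 50% | 0.47 | 0.59 |
| 75% | 0.54 | 0.72 |
| 100% | 0.61–0.62 | 0.85 |

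Attenuation starts with small shares. The value crosses 0.50 at about one third for a 2 SD boost and about 60% for a 1 SD boost. Results with 80% infected are similar.

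**4. Duration cut.** For a normal outcome (for example log duration) with proportion p above the cut c, the efficiency relative to the continuous comparison is φ(c)²/[p(1−p)]. This gives 0.64 for p = 0.5, 0.58 for p = 0.3 and 0.49 for p = 0.2.

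As an illustration, take 130 v 65 symptomatic cases and a 0.4 SD difference (both assumed), two-sided 0.05:

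- **In days:** 0.4 × √(130×65/195) = 2.63. Multiplying by √(3/π) for the Mann-Whitney test gives 2.57, and Φ(2.57 − 1.96) = 0.73.
- **Median cut:** 0.50 v 0.655. The standard error is √(0.25/65 + 0.226/130) = 0.0747, so z = 2.08 and Φ(2.08 − 1.96) = 0.55.

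**The case against.** Several points against the concern have force.

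- **Overlap is not demonstrated.** A participant first dosed on 1 July 2021 completes the month-16 window by 16 November 2022. Follow-up to month 19 without a scheduled titre is compatible with infections being ascertained after the last sample. This stands, and it makes the point conditional. But for every month-16 window to clear 1 December, all first doses (target 300, two hospitals) would have to fall within about two weeks of 1 July, and the protocol does not say so.
- **A reader might infer that the association will be reversed.** The documents do not support that. Reversal needs a large share of post-infection samples and a sizeable boost, and neither is given. Attenuation is the safer expectation.
- **A reader might also infer a definite inflation of month-16 titres.** A 5-fold boost in 20% of samples (both assumed) raises a geometric mean by 5^0.2 = 1.38. But the protocol plans medians for neutralizing and anti-RBD titres, and the median rises about 1.24 to 1.32-fold for an SD of ln titre from 0.7 to 1.3. The between-group comparison is biased only if the post-infection shares differ, which is not shown.
- **The analysis is exploratory.** Breakthrough infection is not a listed endpoint, and the visit might be named in a statistical analysis plan not shown here. That limits the severity. Still, the protocol already fixes the population, test and summaries here, and it leaves open the element on which the interpretation depends.
- **The 7-day class is readable.** This is fair. It is an inefficient choice, not an error, and it can stay as a description.

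**Conclusion.** The point holds as a gap in the specification. Items (4) and (5) of the breakthrough analysis and item (1) of the pseudovirus analysis relate outcomes to titres that need not precede infection, and no analysis-set rule repairs this. With a December 2022 wave assumed, the exposed participants are those first dosed after about mid-July 2021. Their number cannot be derived because no end of enrolment is stated. The likely harm is a weakened protective association, with reversal only if the affected share is large (about a third at a 2 SD boost, about 60% at 1 SD, under the assumed model). An effect on the month-16 group comparison is possible but not shown.

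The duration cut is a lesser point. Under normality it keeps at most about 64% of the information, or about 55% against 73% power in the assumed example. Both matters should be changed; neither touches the primary safety analysis.

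**What to change.** 1. **Infection and symptom analyses (items (4) and (5), and pVNT50 item (1)).** For infected participants use the last scheduled titre drawn before infection onset, and for uninfected participants the same scheduled visit. Where that visit differs between infected participants, make the comparison visit by visit. If onset dates are unavailable, use one common visit before the wave, such as month 13, which clears 1 December 2022 for first doses up to about mid-October 2021. Do not add days from sample to infection as a covariate: it is undefined for the uninfected, and the Mann-Whitney test takes no covariate.
2. **Month-16 immunogenicity.** Keep the planned analysis. Add a sensitivity analysis that flags or excludes samples taken after a confirmed infection. State that exclusion is itself selective: if participants with low titres are infected more often, removing them can overstate persistence.
3. **Symptom duration.** In item (3) compare days between groups by Mann-Whitney or log-rank test. In item (5) relate days to titre by Spearman correlation. Keep longer than 7 days as a descriptive row.
4. **Dates.** State the end of enrolment and the calendar period in which infections are counted.

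The cost is revised wording and a little more analysis. The main dependence is on onset dates: section 3.11 records them for adverse events, but the protocol does not say explicitly that they are collected for infections. If no sample followed an infection, the timing rule removes no titre for that reason; it then only settles which visit is used.
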